### Variables

The demographics of participants include sex, age, and nationality. Personal factors consist of marital status, education level, personality traits, and health status. Work-related factors such as work experience as an OR nurse, professional title, annual income, and hospital tenure are also considered. Additional variables used to describe the sample are satisfaction with salary (does not meet expectations, meet expectations, or far exceed expectations) and average hours of noise exposure per day. The item “What personality traits do you think you belong to?” will be used for personality traits assessment and the answers include stability, emotionality, extroversion, introversion, and psychosis [28]. Furthermore, a self-reported assessment of the population’s health status will be made as “not very healthy” (suffering from severe disease), “fair” (having chronic disease), “healthy” and “very healthy”.

The noise annoyance level of the subjects will be measured by the descriptive rating scale recommended by GB/Z 21233-2007 called “Acoustics—Assessment of noise annoyance by means of social and socio-acoustics surveys” [29], which is the Chinese version of the International Organization for Standardization Technical Specification (ISO/TS) 15666 (2003) [30]. The item is: “Thinking about the last month or so, when you were here working, how much did the noise from the operating room bother, disturb, or annoy you” (not at all = 1, slightly = 2, moderately = 3, very = 4, or extremely = 5)? According to the description of the factors that cause noise in “AORN Position Statement on Managing Distractions and Noise During Perioperative Patient Care” [31], we will measure the annoyance caused by five noise sources, including equipment operations and troubleshooting, behavioral activities, metal instruments and movable equipment of ORs to OR nurses. We consider an overall average score of 4 and above as high annoyance [10]. The measure’s Cronbach’s alpha value was 0.947 in pilot survey of this study.

The Emotional Labor Scale (ELS) will adopt the three-dimensional structural scale of emotional labor proposed by Chinese scholar Luo Hong based on Grandey’s version [32], combined with the actual situation of Chinese clinical nursing, and it has reasonable reliability when used in nurse groups. The scale includes three dimensionality: surface acting (7 items), deep acting (3 items), and natural emotional expression (4 items), with a total of 14 items. The questionnaire’s Cronbach’s alpha value for the three dimensions are 0.711, 0.826 and 0.872, respectively [33], and 0.838, 0.858, and 0.713 respectively in pilot survey of this current study. A 6-point scoring method is used, and from strongly disagree to strongly agree is given 1–6 points in turn; the higher the score, the more times the individual feels emotional adjustment. The total average score of items <2 is considered low-level emotional labor, 2–4 is considered medium-level emotional labor, and > 4 is considered high-level emotional labor.

This study will use the MBI-HSS (MBI Human Services Survey) scale translated and revised by scholars at the Hong Kong Polytechnic University for the nursing population [34]. The Cronbach’s alpha coefficients for each dimension of the questionnaire are between 0.80 and 0.85, and 0.950, 0.923, and 0.953 respectively in pilot survey of our research. The scale has a total of 22 items and 3 dimensions (emotional exhaustion, depersonalization, and personal accomplishment). The evaluation adopts a 7-point Likert scale, with “never”, “rarely”, “occasionally”, “often”, “frequently”, “very frequently”, and “daily” scoring 0–6 points, respectively. We define that a score above or equal to 27 on the emotional exhaustion dimension, above or equal to 8 on the depersonalization dimension, or below or equal to 24 on the personal fulfillment dimension is positive [35]. Additionally, the scores of the three dimensions all lower than the threshold value are considered to be without burnout; the score of one dimension higher than the threshold value is viewed as mild burnout; the score of each of the two dimensions higher than the threshold value is viewed as moderate burnout; and the scores of the three dimensions higher than the critical value is viewed as severe burnout [35]. Besides, the total incidence rate of OR nurse burnout = [(number of people with mild burnout + number of people with moderate burnout + number of people with severe burnout)/ total number of people] × 100% [36]. Since burnout is measured on a continuous scale, we consider that a higher score reflects more severe symptoms of burnout [37].

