Emotional labor (EL) refers to the process by which individuals regulate their emotions to align with organizational expectations, resulting in specific facial expressions and behavioral displays required by their roles [13]. OR nurses frequently engage in emotional labor to provide patient care [14]. Bartram confirmed that emotional labor is a significant positive predictor of burnout [15]. And negative emotions are one of the factors influencing emotional labor [16]. Since noise annoyance is a form of negative emotion [12], the relationship between noise annoyance and emotional labor in OR nurses has yet to be explored.

While the relationship between emotional labor and burnout appears well-established, the link between noise annoyance and burnout remains unclear, and the role of emotional labor in the connection between noise annoyance and burnout is still unknown. Therefore, the objectives of this study are: (1) to investigate the independent correlation between noise annoyance and burnout among OR nurses; (2) to explore the relationship between noise annoyance, emotional labor, and burnout.

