### Participants

Participants will be recruited from 11 hospitals in accordance with the criteria below. The inclusion criteria are: (1) Registered nurses who have worked in ORs for more than 1 year; (2) They should work in the corresponding post in ORs during the investigation period; (3) They provide informed consents and voluntary participation in this study. Visiting fellowship nurses and practical nurses will be excluded in our study.

The required sample size was calculated using G*Power 3.1.9.7 software [26] for multiple linear regression analysis, with four predictor variables: noise annoyance, surface acting, deep acting, and natural emotional expression, and burnout as the outcome variable. While emotional labor is our primary construct of interest, it is operationalized through three distinct dimensions—surface acting, deep acting, and natural emotional expression—each serving as an individual predictor. This differentiation allows for a more nuanced examination of how each aspect of emotional labor contributes to burnout among OR nurses.

The test family used was F-tests, and the statistical test employed was linear multiple regression (Fixed model, R² deviation from zero). A priori: Compute required sample size - given α, power, and effect size, was used for the type of power analysis. Assuming a medium effect size (f² = 0.15), an alpha level of 0.05, and a desired power of 0.95, the minimum required sample size was determined to be 129 participants. To account for a potential 20% dropout rate, the final minimum sample size was calculated to be 155. This sample size ensures sufficient power to detect significant relationships within our multiple regression model [27].

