Potential confounders as contributors to burnout, and possibly related to noise annoyance and emotional labor, were defined a priori and incorporated into the statistical model, such as sex, age, marital status, education level, personality traits, health status, work experience as an operating room nurse, professional title, annual income, satisfaction with salary and hospital tenure. We will carry out linear multiple regression analysis to control for confounders and determine whether noise annoyance and emotional labor are contributors to burnout. Before performing multiple regression analyses, we will examine scatterplots of each predictor variable against the burnout score to check for linear relationships. The normality of residuals will be tested using the Shapiro-Wilk test and visualized with Q-Q plots. And we will evaluate homoscedasticity by plotting residuals versus predicted values. The Durbin-Watson statistic will be used to test for autocorrelation of residuals. In case non-linear relationships are identified, we will consider applying transformations to the predictor variables or incorporating polynomial or interaction terms into the regression model to better capture the nature of the relationships.

To address the risk of multicollinearity arising from multiple confounders, we will calculate Variance Inflation Factors (VIF) and tolerance levels for each predictor variable. A VIF value exceeding 5 or a tolerance value below 0.2 will indicate significant multicollinearity [39]. If multicollinearity is detected, we will consider removing highly correlated variables.

We will use Model 4 (PROCESS macro) in SPSS 26.0 to examine the mediation effect of emotional labor on the relationship between noise annoyance and burnout among OR nurses [40]. A nonparametric, bias-corrected 95% bootstrapped confidence interval (BCI) with 5,000 bootstrap iterations will be used to determine the importance of mediating effects. Indirect effects will be deemed significant if the 95% BCI do not contain zero [41,42]. A p-value of 0.05 or lower will be regarded as statistically significant, based on a two-sided test.

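### Daily hours of noise exposure is collected but not among the named confounders, so the independent annoyance effect may be partly confounded; the VIF rule leaves the a-priori model data-dependent

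*Protocol article*

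**What the plan says.** Aim 1 (Introduction) is "to investigate the independent correlation between noise annoyance and burnout among OR nurses". Under Variables, two items are introduced together as descriptive: "Additional variables used to describe the sample are satisfaction with salary" and "average hours of noise exposure per day".

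Under Statistical analysis, the potential confounders "were defined a priori and incorporated into the statistical model, such as sex, age, marital status, education level, personality traits, health status", and the list goes on with "work experience as an operating room nurse, professional title, annual income, satisfaction with salary and hospital tenure". That makes 11 named variables. Satisfaction with salary is one of them. Exposure hours is not, and no reason is given.

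The same section computes a VIF and tolerance for each predictor and sets the limit: "A VIF value exceeding 5 or a tolerance value below 0.2 will indicate significant multicollinearity". The consequence is: "If multicollinearity is detected, we will consider removing highly correlated variables". The text does not say which variable of a correlated set would go, or that any is exempt. The Participants section identifies the predictors the study is about: the sample size was calculated "with four predictor variables: noise annoyance, surface acting, deep acting, and natural emotional expression".

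**The concern.** Aim 1 is about annoyance itself, apart from other contributors to burnout. Of the variables the article lists, exposure hours is the only one that measures how much noise a nurse is in. The article's own reasoning gives hours a route to burnout that bypasses annoyance. The Introduction ties burnout in operating room nurses to the intensity and overload of the work, and the Research hypothesis section treats noise as a workplace stressor whose stress predicts burnout. None of the 11 named confounders measures current daily workload. Bias control relies on all hospitals being tertiary and in one province to make workloads alike, but that does not equalise daily hours between nurses. If hours is left out, part of what is reported as the effect of being annoyed may be the effect of working longer in noise.

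The VIF rule raises a different problem. Confounders said to be fixed in advance can be dropped after the data are seen, and so, as written, can noise annoyance or an emotional labor dimension. Overlap among confounders alone, such as between age, operating room experience and tenure, does not harm the annoyance estimate. Removing one therefore gains little for Aim 1 and leaves the adjustment set unfixed.

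**Working it through.** **Inputs from the article.** Minimum N = 129 (f² = 0.15, alpha 0.05, power 0.95, four predictors); 11 named confounders; VIF limit 5. The article gives no correlation between hours, annoyance and burnout, so every correlation and slope below is an assumption.

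**The plan's own figure.** Overall F test with 4 and N − 5 df and noncentrality 0.15 × N: the smallest N with power of at least 0.95 is 129 (power 0.9506). The stated 129 reproduces, and this point does not dispute it.

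**Leaving out hours.** Use standardised variables and suppose annoyance has no effect of its own. The annoyance slope without hours is then

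bias = r(hours, annoyance) × r(hours, burnout).

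The two-sided rejection rate at N = 129 follows from the normal approximation with noncentrality r/√(1 − r²) × √129, where √129 = 11.36:

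| r(hours, annoyance) | r(hours, burnout) | spurious r | noncentrality | rejection rate |
|---|---|---|---|---|
| 0.2 | 0.2 | 0.04 | 0.45 | about 7% |
| 0.3 | 0.3 | 0.09 | 1.03 | about 18% |
| 0.4 | 0.3 | 0.12 | 1.37 | about 28% |

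The Fisher z approximation gives 7.3%, 17.3% and 27.3%. Over a wider grid (r(hours, annoyance) 0.1 to 0.5, hours slope on burnout 0 to 0.3) the bias runs from 0.00 to 0.15 SD and the rejection rate from 5% to about 40%. Wherever the direct hours slope is 0, the bias is 0 and the rate stays at 5%.

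This is a three-variable illustration without covariates. In the planned regression, only the hours–annoyance and hours–burnout associations that remain after the other covariates count, and these may be smaller.

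**The VIF rule.** VIF = 1/(1 − R²), so VIF above 5 needs R² above 0.80, or with a single partner variable a correlation above √0.80 = 0.894. Take two confounders correlated at 0.90: VIF = 1/(1 − 0.81) = 5.26. Suppose the one that matters is dropped and its near-duplicate kept. With g its slope on burnout and a its correlation with annoyance, the left-over bias in the annoyance slope is

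g × a × (1 − 0.81) / (1 − 0.81 × a²).

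- g = a = 0.1: 0.01 × 0.19 / 0.9919 = 0.002 SD (both left out: 0.01)
- g = a = 0.3: 0.09 × 0.19 / 0.9271 = 0.018 SD (both left out: 0.09)

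The kept variable does most of the adjusting.

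**Cost of adding hours.** Counting each confounder as one term, the model has 4 + 11 = 15 predictors, or 16 with hours. For a 4-df test of the four core predictors at f² = 0.15, read as a partial effect, N for 0.95 power is 130 in both cases.

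**The case against.** The omission is inferred. The words introducing the confounders mark the list as examples, and the descriptive label under Variables does not bar a variable from the model, since satisfaction with salary carries the same label and is included. This stands: hours is missing from the named list, not expressly excluded. But an open-ended list sits badly with confounders said to be set in advance.

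The causal position of hours is uncertain. It may act on burnout only through annoyance, in which case leaving it out causes no bias. It is also self-reported in the same cross-sectional questionnaire as annoyance, so an annoyed nurse may report more noise hours; adjusting could then remove part of the effect of interest. This stands too, and it is why results with and without hours are needed, not one adjusted figure alone.

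The illustration ignores the planned covariates and rests on assumed correlations, and its lowest case is close to the nominal 5%. That limits it to showing that the bias could matter.

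On VIF, removal is only to be considered, and a variable over the limit is largely redundant with those kept. This answers the worry about bias. It does not answer the lack of a fixed model, or the lack of protection for the variables the hypotheses concern.

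A full protocol or analysis plan may hold a closed list. The point here is about what the article itself states: the named list, the descriptive role of hours, and the removal rule.

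**Conclusion.** The point holds as a risk that the plan can cheaply remove. Hours of noise exposure is collected, plausibly relates to both annoyance and burnout, and is not among the named confounders, so the annoyance coefficient may be partly confounded. The size cannot be derived from the article: about 7% to 28% false positives at N = 129 under assumed correlations of 0.2 to 0.4 without covariates, probably less with them, and no excess if hours works only through annoyance.

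A reader might infer that the independent effect is certain to be confounded, or that the VIF rule will strip out confounders and bias it. The documents support neither. They do not settle whether hours has its own path to burnout, removal is discretionary, and dropping one of two near-duplicates leaves about 0.002 to 0.018 SD under the assumptions used. What they do show is an adjustment set described as fixed in advance that is open in its wording and changeable by the data, with no protection for noise annoyance or the emotional labor dimensions.

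**What to change.** 1. Replace the open-ended list with a closed list of confounders.
2. Add average daily hours of noise exposure to that list, for both the multiple regression and Model 4. Report the annoyance coefficient and the indirect effects with and without it, and state in advance which is the main result. Explain that hours is self-reported and its causal position uncertain.
3. Delete the sentence on removing highly correlated variables. Keep all a-priori confounders, noise annoyance and the three emotional labor dimensions whatever their VIF, and report VIFs as a diagnostic only.

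The cost is 1 df for a variable already on the questionnaire, a slightly wider interval if hours tracks annoyance closely, and one extra set of results. On the 4-df calculation above, adding hours leaves the required N unchanged at 130.

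### The burnout severity rule counts scores above the threshold on all three dimensions, although personal accomplishment is positive when low, so every grade is off by one level as written

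*Protocol article*

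**What the plan says.** All of the relevant text is in the paragraph on the MBI-HSS in the Protocol article, Materials and methods, Variables.

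- **Positivity.** Two dimensions are positive when high: "a score above or equal to 27 on the emotional exhaustion dimension, above or equal to 8 on the depersonalization dimension". The third is positive when low: "below or equal to 24 on the personal fulfillment dimension is positive". The dimension called fulfillment there is taken to be the one listed as personal accomplishment just before it.
- **Grading.** No burnout: "the scores of the three dimensions all lower than the threshold value are considered to be without burnout". Mild: "the score of one dimension higher than the threshold value is viewed as mild burnout". Moderate: "the score of each of the two dimensions higher than the threshold value is viewed as moderate burnout". Severe: "the scores of the three dimensions higher than the critical value is viewed as severe burnout". No exception is made for accomplishment.
- **Burnout rate.** The numerator is "number of people with mild burnout + number of people with moderate burnout + number of people with severe burnout", divided by all respondents.
- **Continuous score.** Items are scored 0 to 6 by frequency, with no reversal mentioned, and "we consider that a higher score reflects more severe symptoms of burnout".

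The Participants section names burnout as the outcome of the sample-size regression. Statistical analysis uses a burnout score in the regression and burnout as the outcome of the mediation model. The article does not say how the three dimensions form that score.

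**The concern.** The definition of a positive dimension and the grading rule cannot both be applied. On accomplishment, the first puts the burned-out side at or below 24, while the second puts it above the threshold. An analyst who codes the grading sentence as printed will count high accomplishment as a sign of burnout and low accomplishment as its absence. Every severity grade, and the burnout rate built from the grades, is then affected.

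The same question of direction reaches the continuous outcome. If accomplishment were added to the other two dimensions without reversal, it would offset them, and the associations in hypotheses a, c and d would be measured against a blunted outcome.

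**Working it through.** **Inputs from the article:** cut-points of 27 or more (exhaustion, EE), 8 or more (depersonalization, DP) and 24 or less (accomplishment, PA); the four grading clauses; the rate formula; item scores of 0 to 6. The article gives no burnout rate, mean, SD or correlation, so there is no figure of its own to reproduce on this point. Its sample size of 129 does reproduce (power 0.951 at 129, 0.949 at 128) and does not depend on the grading.

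**1. Two nurses**
- EE 10, DP 3, PA 40: no dimension is positive. Literally, PA is above 24, so one score is higher: mild.
- EE 20, DP 5, PA 20: PA is positive, so one positive dimension. Literally, all three are lower: no burnout.

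**2. All patterns.** Let E, D and P be 1 if the dimension is positive and 0 if not. Away from ties, the count of positive dimensions is E + D + P. The literal count of scores above the threshold is E + D + (1 − P). The difference, literal minus positive, is 1 − 2P: +1 when accomplishment is healthy and −1 when it is not. It is never 0.

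| EE | DP | PA | By positive dimensions | Literal |
|---|---|---|---|---|
| − | − | >24 | none | mild |
| − | − | <24 | mild | none |
| − | + | >24 | mild | moderate |
| − | + | <24 | moderate | mild |
| + | − | >24 | mild | moderate |
| + | − | <24 | moderate | mild |
| + | + | >24 | moderate | severe |
| + | + | <24 | severe | moderate |

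**3. Ties.** Scores of exactly 27, 8 or 24 are positive by definition but neither higher nor lower than the threshold. EE 20, DP 5, PA 24, for example, receives no grade.

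**4. Effect on the rate.** With positive rates e, d and p, and independence assumed, the rate is 1 − (1−e)(1−d)(1−p) by the cut-points and 1 − (1−e)(1−d)p literally. The difference, cut-points minus literal, is (1−e)(1−d)(2p−1). Its sign therefore turns on whether p is above or below 50%.
- e = d = p = 0.3: 1 − 0.7×0.7×0.7 = 65.7%, against 1 − 0.7×0.7×0.3 = 85.3%.
- e = 0.6, d = 0.5, p = 0.7: 1 − 0.4×0.5×0.3 = 94.0%, against 1 − 0.4×0.5×0.7 = 86.0%.
- e = 0.5, d = 0.4, p = 0.5: 85.0% both ways.

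The next table drops independence. It uses 400,000 simulated normal score triples, rounded and clipped to assumed ranges of 0–54, 0–30 and 0–48. The assumed SDs are 11, 6 and 9, with correlations of 0.6 (EE–DP) and −0.3 (PA with each). Ties are counted as not higher.

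| Assumed means EE/DP/PA | Rate by cut-points | Rate literally |
|---|---|---|
| 25/7/30 | 67% | 92% |
| 25/7/22 | 80% | 77% |
| 20/5/20 | 78% | 62% |

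In the first row the grade differs for about 93% of nurses. The rest agree only because a tie on EE or DP offsets the error on PA.

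**5. Continuous score, if PA were added unreversed.** The correlation of annoyance with a total is Σ(w·r·s) / √(wᵀCw), where s are the SDs, C is the covariance matrix and w is (1, 1, −1) reversed or (1, 1, 1) unreversed. The assumed correlations of annoyance with EE, DP and PA are 0.3, 0.3 and −0.2, and EE–DP is 0.6.
- SDs 11, 6, 9; PA correlation −0.3 with each: reversed (3.3 + 1.8 + 1.8)/√409.0 = 0.34; unreversed (3.3 + 1.8 − 1.8)/√225.4 = 0.22.
- SDs 11, 6, 5; PA correlation −0.5 with each: reversed (3.3 + 1.8 + 1.0)/√346.2 = 0.33; unreversed (3.3 + 1.8 − 1.0)/√176.2 = 0.31.

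These are two illustrations, not bounds.

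**The case against.** The best reply is that the grading sentence directly follows the definition of positivity and carries the same citation, so being above the threshold is loose wording for being positive. That may well be what the authors intend, and if they code it so, the grades come out right. It does not make the printed rule correct: the rule speaks of scores being higher and lower and exempts no dimension. Assuming that accomplishment is already reverse-scored does not rescue it either, because 24 or less would then be the healthy side and the positivity sentence would be wrong instead.

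Three stronger readings are tempting, and the article does not support them.

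- **That the regression outcome is wrong.** Nowhere does the article say that an unreversed total will be formed. The statement that higher means worse can be read as fixing the direction of the outcome, which would itself require reversal, and a condensed article may leave item recoding to a fuller document. What stands is that 0-to-6 scoring without reversal, low accomplishment as the positive side, and higher meaning worse cannot all hold for one score that includes accomplishment.
- **That the burnout rate will be inflated.** It may be inflated, deflated or unchanged, depending on how many nurses fall at or below 24 on accomplishment.
- **That the main results or all hypotheses are affected.** Both aims concern associations, and Statistical analysis names no analysis of the grades or the rate. Hypothesis b relates noise annoyance to emotional labor and does not involve burnout.

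**Conclusion.** The grading rule is wrong as written. This follows from the article's own text and needs no outside figure: away from ties at the cut-points, every pattern is misgraded by exactly one level, and scores at 27, 8 or 24 are covered by neither the higher nor the lower wording. The burnout rate inherits the error. The size and sign of that effect are not determined by the article; the gaps shown, from 25 points upward to 16 points downward, rest on assumed distributions. Even where the rate happens to agree, the individual grades do not.

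The continuous score is a secondary and less certain matter: its direction and construction are unresolved rather than shown to be wrong. If accomplishment did enter unreversed, the association of noise annoyance with burnout (hypotheses a and d) would be attenuated, slightly or substantially depending on the assumed SDs and correlations. The association of emotional labor with burnout (hypothesis c) would be exposed in the same way.

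**What to change.** 1. Replace the grading sentence with a count of positive dimensions under the article's own cut-points (exhaustion 27 or more, depersonalization 8 or more, accomplishment 24 or less): 0 none, 1 mild, 2 moderate, 3 severe. This also settles the ties.
2. State that the accomplishment items are reverse-scored (6 minus the item score) before any total burnout score is formed for the regression and mediation, and report the three dimensions beside that total. Keep the unreversed accomplishment score for the cut-point of 24.

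The cost is two sentences in the protocol and one recode in SPSS. No new data are needed.
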